## Methods

### Design

This is a double-blinded randomized placebo-controlled phase II trial of anakinra in patients diagnosed as having dengue with warning signs/severe dengue and hyperferritinaemia (>2000 ng/ml) (
Figure 1). The study will enrol 160 adults and children ≥ 12 years old admitted to the Hospital for Tropical Diseases, Ho Chi Minh City. Participants will be randomized 1:1 (anakinra:placebo) on electronic database system (Ennov) and stratified according to the ward of recruitment (Intensive Care Units/Emergency Department or the general dengue wards). Patients with warning signs or severe dengue (defined by 2009 WHO classification) and ferritin > 2000 ng/ml will be eligible for enrolment.

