### Secondary endpoints

The secondary endpoints are: 30-day mortality; change in mSOFA score at day 7 post randomization; number of days in ICU; number of days in hospital; number of individuals with serious adverse events (time-period 1–5 days and 6–30 days); number of adverse events per individual during the whole study course; change in ALT and platelets over 5 days following randomization; change in ferritin and CRP levels over 5 days following randomization and until day 30 after illness onset; time to normalization of platelets (defined as >150 ×10
^9^/l) and neutrophils (>2 ×10
^9^/l); platelet nadir; fever clearance time (defined as <37.5 °C for at least 48 hours; measured 4 times/day); duration of viraemia (number of days to first negative qPCR and NS1); AUC viraemia (from enrolment to negative); EQ-5D-5L questionnaire score at hospital discharge and day 30.

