### Randomization

After confirmation of eligibility, including obtaining ICF for randomization phase, study doctors will perform randomization on the electronic data system (Ennov). Randomization will be minimization at 1:1 ratio and stratified according to the ward of recruitment. The system will assign a unique study ID and drug code for the patient. The assigned drug code will correspond to a sealed pre-packaged box containing 08 doses (bd dosing for 4 days) of either anakinra or visually matched placebo for adults or children. Drug appearance and administration schedules will be identical to maintain blinding amongst the attending physicians and nurses. Neither the patients nor the study assessors, including treating physicians, study doctors/nurses, know which group patients in.

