### Data collection

Study data will be collected using an electronic CRF, except identification information which will only be recorded on paper CRF. All patients will be reviewed daily until discharge. Standardized clinical information and a full blood count, biochemistry and research blood sampling will be performed at each visit, plus any other tests deemed necessary by the attending physician. Details of all adverse events will be recorded on specific forms. An ultrasound scan of the chest and abdomen to assess vascular leakage will also be performed on alternate days in all participants by a study staff member using the portable ultrasound scan machine provided by OUCRU.

During the follow-up visits at day 30 and 3-months after the fever onset, patients will be asked about any newly emerging or persisting symptoms using a standardized questionnaire. Research blood samples will be taken for convalescent serology, immunology studies, full blood count and biochemistry tests.

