### Statistical considerations

**
*Sample size.*
** Given that delta mSOFA score has an approximately normal distribution
^
25
^ with a standard deviation of 2.4, which was based on a cohort of 38 adults admitted with severe dengue, we would need a sample size of 80 patients per group to detect a between-group difference of at least 1.0 point with 80% power and 5% type-I error rate.

**
*Statistical analysis.*
** The primary endpoint (delta mSOFA score) and the secondary endpoints (ALT, CRP, PLTs and ferritin) will be analyzed using a linear mixed-effects model, which models their values over the first 4 days for mSOFA and 5 days for lab tests (as specified in sections 2.4.1 and 2.4.2). We will use a linear trend for time as fixed and random effects. The slope of this model reflects the change in value over time. Therefore, the effect of anakinra is measured as the difference in slope between treatment groups. This difference will be assessed via the interaction between time and treatment group in that model, and presented with a corresponding 95% confidence interval. For the change at day 30 (ferritin and CRP) we will use the difference with the value at randomisation. Mortality will be assessed by comparing Kaplan-Meier curves via log-rank test. The number of serious adverse events will be compared via 2×2 tables with chi-square tests, or Fisher’s exact test in case the expected number under the null hypothesis is smaller than 1 in at least one of the cells. Number of AEs per individual will be compared using Poisson regression, or quasi-Poisson regression in case of overdispersion. EQ visual analogue score will be compared via linear regression in case it has a fairly symmetric distribution; otherwise we will use beta-regression. Normalization of neutrophils will be defined as first time to reach normal range of >2.0 ×10
^9^/l and for platelets the first time to reach >150 ×10
^9^/l and will be assessed by Cox model. For viraemia AUC and duration outcomes we will also perform the analysis with correction for day of illness (DOI). The time of fever clearance is defined by the first time after which all readings are <37.5°C in the following 48 hours.

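### The Cox analysis of time to platelet and neutrophil normalization names neither the entry count nor the ward stratum; a treatment-only model would be valid but less efficient than one the trial can already fit

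*Protocol article*

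**What the plan says.** All references are to the protocol article.

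- **Endpoint.** Secondary endpoints lists "time to normalization of platelets (defined as >150" and a matching neutrophil endpoint with a threshold of 2 (both ×10⁹/l).
- **Analysis.** Statistical considerations gives the event definitions, "Normalization of neutrophils will be defined as first time to reach normal range of >2.0" and "for platelets the first time to reach >150", and then the method: "and will be assessed by Cox model". Nothing more is said about that model.
- **Covariates elsewhere in the paragraph.** The next sentence reads: "For viraemia AUC and duration outcomes we will also perform the analysis with correction for day of illness (DOI". This is the only covariate correction named there.
- **Allocation.** Design describes randomisation as "stratified according to the ward of recruitment (Intensive Care Units/Emergency Department or the general dengue wards", and Randomization says: "Randomization will be minimization at 1:1 ratio and stratified according to the ward of recruitment".
- **Availability of the entry count.** Data collection says: "Standardized clinical information and a full blood count, biochemistry and research blood sampling will be performed at each visit". The exclusion of patients with neutrophils below 1.0 also requires a count before entry.

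**The concern.** The event is a blood count crossing a fixed threshold. Where that same count starts is the obvious candidate for the main predictor of how long the crossing takes. The inclusion and exclusion criteria set no platelet limit and exclude only neutrophils below 1.0, so entry counts may vary widely. Ward separates intensive care and emergency patients from general-ward patients, and it was judged important enough to stratify the randomisation.

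If the Cox model contains treatment alone, two things follow when these variables are prognostic. The comparison has less power than one that uses them. The hazard ratio it estimates is also a marginal one, which lies nearer 1 than the hazard ratio conditional on the entry count. At stake is the chance of detecting an effect of anakinra on haematological recovery, using data the trial collects anyway.

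**Working it through.** **No plan figure to reproduce.** The only power statement in the article (80 per group, 80% power) is for delta mSOFA. None is given for the normalization endpoints.

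**Inputs from the documents.** 160 patients, 1:1, stratified by a two-level ward factor.

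**Assumed inputs, because the documents give none.** Conditional hazard ratio 1.5 for normalization (above 1 means faster recovery); exponential times; 40% of patients in one ward stratum; entry count as a standard-normal covariate with a log hazard ratio of 0 to 1.0 per SD; ward log hazard ratio of 0 to −0.7; 20% or 50% of patients censored.

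**Step 1: scale.** With d events and 1:1 allocation, Schoenfeld's approximation is

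power = Φ(√d × ln(HR) / 2 − 1.96).

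For HR 1.5, ln(1.5) = 0.405.

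- d = 160 (no censoring): 12.65 × 0.405 / 2 − 1.96 = 0.60, power 73%.
- d = 128 (20% censored): 11.31 × 0.405 / 2 − 1.96 = 0.33, power 63%.
- d = 80 (50% censored): 8.94 × 0.405 / 2 − 1.96 = −0.15, power 44%.

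This is roughly the power available once the predictors are in the model.

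**Step 2: cost of leaving them out.** Simulation with 1,500 trials per setting and two-sided 5% tests compared a treatment-only Cox model with one that adds entry count and ward as covariates.

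20% censored:

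| Entry count log-HR per SD; ward log-HR | HR, treatment only | HR, adjusted | Power, treatment only | Power, adjusted | Loss (points) |
|---|---|---|---|---|---|
| 0; 0 | 1.51 | 1.52 | 63.9% | 64.2% | 0.3 |
| 0.25; 0 | 1.49 | 1.52 | 60.1% | 64.9% | 4.8 |
| 0.5; −0.4 | 1.43 | 1.51 | 49.7% | 62.7% | 13.0 |
| 0.8; −0.4 | 1.36 | 1.51 | 39.4% | 62.7% | 23.3 |
| 1.0; −0.7 | 1.31 | 1.50 | 31.8% | 62.6% | 30.8 |

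50% censored:

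| Entry count log-HR per SD; ward log-HR | HR, treatment only | HR, adjusted | Power, treatment only | Power, adjusted | Loss (points) |
|---|---|---|---|---|---|
| 0; 0 | 1.49 | 1.50 | 42.6% | 42.7% | 0.1 |
| 0.25; 0 | 1.49 | 1.51 | 42.6% | 44.7% | 2.1 |
| 0.5; −0.4 | 1.44 | 1.49 | 35.7% | 42.4% | 6.7 |
| 0.8; −0.4 | 1.40 | 1.50 | 32.4% | 41.8% | 9.4 |
| 1.0; −0.7 | 1.37 | 1.52 | 28.1% | 44.5% | 16.4 |

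The simulation standard error of a single power figure is at most √(0.5 × 0.5 / 1500) = 1.3 points.

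**Step 3: type I error.** With a true hazard ratio of 1.0, the treatment-only test rejected in 3.7% to 5.2% of runs across the ten settings, and the adjusted test in 4.7% to 6.5%. The simulation standard error here is √(0.05 × 0.95 / 1500) = 0.6 points. The treatment-only test is not inflated. The adjusted test is close to nominal, with 6.5% in one setting and at most 5.4% in the other nine.

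**Limits.** Ward has no separate figure; its effect is mixed with that of the entry count. Ward entered as a covariate, and a ward-stratified Cox model was not simulated.

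**The case against.** **The text is silent rather than wrong.** The article does not say unadjusted or treatment-only. It condenses a fuller document, and covariates for a secondary endpoint are often left to the analysis plan. A reader might infer that the protocol has committed to an unadjusted analysis; the documents do not establish that. The other models in the paragraph list no baseline count or ward either. This stands as a limit on the wording. Two things still favour the treatment-only reading. The paragraph is otherwise specific about fallbacks (Fisher's exact test, quasi-Poisson, beta-regression). It also presents day-of-illness correction as an additional analysis for viraemia only, which suggests that the default is uncorrected.

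**The shift toward 1 is not bias.** A reader might infer that the treatment-only model underestimates the effect. It estimates a different quantity: the hazard ratio is non-collapsible, so the marginal and conditional values differ even under perfect randomisation. Chance imbalance in entry counts is already allowed for in the error rate of the unadjusted test. This stands in full; what remains is efficiency and choice of estimand.

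**The size could easily be overstated.** With no censoring and assumed correlations of 0.3 to 0.7 between entry count and log time, simulated power rises from 62% to 72% at the low end and from 29% to 69% at the high end, a gain of about 10 to 40 points. The documents support neither assumption. Review is daily only until discharge, with the next visit at day 30, so censored or interval-known times are possible. Some patients may enter above 2.0 neutrophils, and platelets may still fall after entry, so the entry count is not simply the distance to the threshold.

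**The endpoints are secondary.** They have no stated power target, and platelets are also analysed by a mixed model over 5 days. This limits the importance of the point but does not remove it.

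**Conclusion.** The point holds as a matter of efficiency. As written, the two normalization endpoints are compared by a Cox model with no named covariate or stratum. If that model is treatment-only, it is a valid test of a marginal hazard ratio. It discards information that is plausibly strongly prognostic and already available.

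For a conditional hazard ratio of 1.5, the loss runs from nil, when neither variable is prognostic, through about 5 to 31 points at 20% censoring. At 50% censoring it is 0 to about 16 points. Every one of these figures rests on assumed covariate effects and censoring. The direction is firmer than the size: adjustment gains power when the entry count matters and costs essentially nothing when it does not.

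The documents do not support a claim of false-positive risk, of a biased estimate, or of any effect on the primary endpoint or trial size. The change is worth making but is not essential.

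**What to change.** Specify each normalization analysis as a Cox model for treatment, adjusted for the log of the relevant count at randomisation (platelets or neutrophils) and stratified by ward of recruitment. Make this the lead result and report the unadjusted hazard ratio beside it. If the analysis plan already says so, no change is needed beyond keeping the two documents consistent.

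The cost is one sentence, written before unblinding. Both variables should already be collected, and no visit, sample or trial procedure changes. Fixing the covariates in advance also prevents a post hoc choice. The small downside is that the lead hazard ratio is conditional on the entry count and must be described that way, which is why the unadjusted estimate should accompany it.

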## Background

Dengue continues to be a major public health burden in Vietnam and globally
^
1
^. While most clinical cases of dengue resolve after 1 week, approximately 5–10% of hospitalized patients will develop severe manifestations, usually during the critical phase (day 4–6 of illness)
^
2
^, allowing a window of opportunity to identify patients at risk of progression and intervene with a disease modifying agent
^
3,
4
^. However, thus far, no antiviral agents or adjunctive therapies have been found to alter disease outcomes in dengue
^
3–
6
^. Novel host directed therapeutics are urgently needed for patients with dengue, particularly those at high risk of developing severe disease.

Understanding of the mechanism underlying progression to severe disease has improved; it has been demonstrated that hypercytokinemia and an excessive host inflammatory response to infection are associated with life-threatening complications
^
2,
3
^. The dengue virus (DENV) replicates within monocytes and macrophages, and failure to clear these virus-infected cells by dysfunctional cytotoxic NK/CD8+ T cells can facilitate a hyperinflammatory state or “cytokine storm”, through persistent macrophage activation and ultimately end-organ damage. Therapeutic trials with broad immunosuppression using corticosteroids in dengue have so far been unsuccessful
^
5
^, likely due to unselected patient populations with insufficient stratification. Interleukin-1 (IL-1) is a key pro-inflammatory cytokine involved in the cytokine storm and also in dengue pathogenesis
^
7–
9
^. One of the safest and possibly most targeted ways of controlling this excessive inflammation is through IL-1 receptor (IL-1R) blockade
^
6
^.

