### Inclusion and exclusion criteria

Patients will be eligible for study enrolment if they: (i) are more than or equal to 12 years of age; (ii) have a clinical diagnosis of dengue and at least one warning sign or severe dengue (based on the World Health Organization (WHO) 2009 or Vietnamese Ministry Of Health (MOH) – Dengue guidelines)
^
23,
24
^; (iii) have plasma ferritin levels > 2000 ng/mL ; (iv) agree to come back for two follow up visits between day 30 – 35 and at around day 90 afterillness onset; and (v) provide written informed consent.

Exclusion criteria include: (i) pregnancy (confirmed by either clinical examination or urine dipstick for human chorionic gonadotropin hormone); (ii) localizing features suggestive of an alternative diagnosis; (iii) taking immunosuppressive drugs or other biologics in the last month; (iv) underlying malignancy or immunosuppression; (v) children less than 12 years of age; (vi) have baseline GFR < 30 ml/min; (vii) having a neutrophil count < 1.0 × 10
^9^/L; (viii) being treated for tuberculosis; (ix) HBsAg-positive; (x) taking any drug with significant interaction with anakinra (concomitant medication and drug interactions); (xi) patients who are considered unlikely to attend follow-up visits because of long travelling distance to the study clinic or other reasons.

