### Screening

Patients hospitalized to one of the study wards of the Hospital for Tropical Diseases (HTD), Ho Chi Minh City, Vietnam with clinically suspected dengue with warning signs/severe dengue will be identified and, if potentially eligible, approached by study staff. If patients agree to participate in the trial and provide the written consent/assent form, they will be screened for eligibility based on the criteria listed in the section above. Initial screening tests include baseline ferritin, creatinine, HBsAg and, in all female patients, a pregnancy test using a urine dipstick.

Potentially eligible patients who have baseline ferritin levels > 1000 ng/ml but ≤ 2000 ng/ml on admission will be invited to continue the screening phase of the trial which lasts for 3 days with daily ferritin testing. If the ferritin level rises to above 2000 ng/ml during this period, and all inclusion criteria are met, the patient will be recruited. If the ferritin remains below the 2000ng/ml threshold after 3 days, the screening phase will end and all study procedures will stop. Patients will also be excluded if their ferritin levels are below 1000ng/ml.

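### Fever clearance time and, less strongly, viraemia duration and AUC do not require fever or viraemia at randomisation, so patients already clear at entry can dilute these secondary comparisons

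*Protocol article*

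**What the plan says.** Fever clearance is defined twice in the protocol article. The Secondary endpoints section has "fever clearance time (defined as <37.5 °C for at least 48 hours; measured 4 times/day", and Statistical considerations has "The time of fever clearance is defined by the first time after which all readings are <37.5°C in the following 48 hours". Threshold, window and reading frequency are therefore fixed. There is no condition that the patient has fever to clear, no stated time origin, and no named test for this endpoint.

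For viraemia, Secondary endpoints lists "duration of viraemia (number of days to first negative qPCR and NS1" and "AUC viraemia (from enrolment to negative". AUC is the only one of these endpoints with a stated start. None requires a positive enrolment sample. Statistical considerations adds one safeguard, for viraemia only: "For viraemia AUC and duration outcomes we will also perform the analysis with correction for day of illness (DOI".

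On who can enter, the Inclusion and exclusion criteria ask that patients "have a clinical diagnosis of dengue and at least one warning sign or severe dengue", together with ferritin above 2000 ng/mL. No current fever, positive qPCR or positive NS1 is required, and there is no limit on day of illness. Under Screening, patients whose admission ferritin is above 1000 but not above 2000 ng/ml may "continue the screening phase of the trial which lasts for 3 days with daily ferritin testing". The Background places severe manifestations "usually during the critical phase (day 4–6 of illness".

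**The concern.** A time-to-clearance endpoint is informative only in patients who have something to clear. Under the 48-hour rule as written, a patient whose readings are all below 37.5°C from randomisation onwards satisfies it at the first reading. A patient whose enrolment sample is negative has no viraemia to follow. Both outcomes are settled before the first dose, so treatment cannot change them, yet nothing in the definitions separates them from clearances that happened on treatment.

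The entry rules make such patients possible: diagnosis is clinical, admission may fall late in the illness, and some patients wait up to 3 days for ferritin to rise. The stake is a diluted result on endpoints close to the proposed mechanism. The article's Discussion names fever among the effects of the IL-1β loop that anakinra targets. A weak result could be read as lack of activity when part of it came from patients in whom no activity could be seen.

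**Working it through.** **Plan's own figure.** There is none for these endpoints. The article's only power statement concerns delta mSOFA and does not bear on this point. Only its group size is used here.

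**Inputs from the article.** 80 per group (Statistical considerations), 1:1 allocation (Design), four temperature readings a day (Secondary endpoints).

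**Assumptions, not in the article.** Clearance times are exponential with mean 2 days on placebo, rounded up to the next of four daily readings. There is no censoring and time runs from randomisation. A share p of patients in both arms is clear at entry and scored 0. The test is a two-sided 5% log-rank test, with a Cox model (Efron ties) for the hazard ratio. The article names neither for fever clearance.

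**Hazard ratio.** The value that 160 events detect with 80% power is exp[(1.960 + 0.842)/√(160 × 0.25)] = exp(2.802/6.325) = exp(0.443) = 1.557.

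**Simulation.** 4,000 trials per row for power; hazard ratios averaged over the first 600.

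| Share clear at entry | Power, all patients | Power, not clear at entry | HR, all | HR, not clear at entry |
|---|---|---|---|---|
| 0% | 80.2% | 80.2% | 1.57 | 1.57 |
| 10% | 68.5% | 73.6% | 1.50 | 1.57 |
| 20% | 58.6% | 68.8% | 1.42 | 1.57 |
| 30% | 49.1% | 64.6% | 1.37 | 1.57 |
| 50% | 31.9% | 49.0% | 1.23 | 1.55 |
| 70% | 18.0% | 32.4% | 1.11 | 1.55 |

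**Hand check at 20%.** 160 × 0.8 = 128 patients have something to clear.

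- Restricted: 0.443 × √(128 × 0.25) = 2.506, and Φ(2.506 − 1.960) = 0.707, against 68.8% simulated.
- All patients: the 32 tied zeros add no signal but add variance of 32 × 0.25 × 128/159 = 6.44. The statistic becomes 0.443 × 32/√(32 + 6.44) = 2.29, and Φ(2.29 − 1.96) = 0.63, against 58.6% simulated.

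This approximation runs a little high in both cases but shows the same ordering and the reason for it.

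**On the mean scale.** If D is the mean difference in patients with something to clear, the difference over all patients is (1 − p) × D: 0.8D at 20% clear and 0.5D at 50%.

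**Direction.** Status at entry precedes treatment, so the zeros fall in both arms by chance alone. With no treatment effect the two arms still have the same distribution. The loss is in power and in the size of the estimate, not in validity.

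**The case against.** The strongest reply is that the article does not say that these patients are scored at time 0. It gives no origin for fever clearance or viraemia duration, and no analysis set. Such details often sit in the full protocol or the analysis plan, which are not shown. This stands in part: time 0 is an inference, and the point is conditional on counting from randomisation. It does not remove the concern, because the published rule is specific on everything except the presence of fever. Counting from illness onset would not help either, since these patients' events would then precede randomisation and be equally beyond the reach of treatment.

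A reader might go further and infer that the plan will hide a real effect, or that the median will be 0 in both arms. The documents do not support either. The mechanism is dilution, and a median of 0 needs more than half of patients clear at entry, for which the article gives no figure. A comparison of all randomised patients is also valid; it answers a different question.

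The viraemia part is weaker. An additional analysis corrected for day of illness is planned, which shows that time of presentation was considered, although it keeps patients who are negative at entry and does not cover fever. The duration endpoint names qPCR and NS1 together. If both must be negative, a patient negative on only one at enrolment does not score 0.

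Finally, restriction recovers only part of the power. The rest of the loss comes from having fewer informative patients.

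**Conclusion.** The point holds as a defect in how secondary endpoints are defined: clearly for fever clearance, less strongly for viraemia duration and AUC. Patients with nothing to clear can be enrolled, and the definitions do not set them apart. If time runs from randomisation, they dilute the comparison. There is no bias towards either arm, no inflation of type I error and no effect on the primary endpoint.

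The size cannot be fixed from the article because the share clear at entry is not reported. Under the stated assumptions, 20% clear at entry costs about 21 percentage points of power (80% to 59%), of which restriction recovers about 10 (to 69%). The estimated hazard ratio falls from about 1.57 to 1.42, and restriction removes that attenuation. At 50% the figures are 32% against 49%, with a hazard ratio of about 1.23. These are illustrations, not forecasts. The change is worth making because it is cheap, provided the analysis plan does not already cover it.

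**What to change.** - State randomisation as the time origin for fever clearance and viraemia duration.
- Analyse fever clearance in patients whose last temperature reading at or before randomisation is 37.5°C or more. A longer look-back, such as any fever in the previous 24 hours, would still admit patients who have already settled and score 0.
- Analyse qPCR duration and viraemia AUC in patients qPCR-positive on the enrolment sample, and NS1 duration in patients NS1-positive on it. This also separates the two tests that the duration endpoint now joins.
- Report the share already clear at entry, by arm, for each endpoint.
- Keep the all-randomised analysis as a sensitivity analysis. It also retains patients who are afebrile at entry but become febrile afterwards.

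Each subset is defined by status before treatment, so the randomised comparison is preserved. The cost is mainly wording: temperature is already measured four times a day and blood is already sampled, though the team should confirm that a reading at or before randomisation is recorded. The downside is an analysis set smaller than 160, with results that apply to patients febrile or viraemic at entry.
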